** Child growth**			
Length-for-age z-score *	X.XX (X.XX)	X.XX (X.XX)	X.XX (X.XX)
Stunting - no.(%)	XXX (XX.X)	XXX (XX.X)	XXX (XX.X)
Weight-for-age z-score *	X.XX (X.XX)	X.XX (X.XX)	X.XX (X.XX)
Underweight - no. (%)	XXX (XX.X)	XXX (XX.X)	XXX (XX.X)
Weight-for-length z-score *	X.XX (X.XX)	X.XX (X.XX)	X.XX (X.XX)
Wasting - no. (%)	XXX (XX.X)	XXX (XX.X)	XXX (XX.X)
Head circumference (cm) *	X.XX (X.XX)	X.XX (X.XX)	X.XX (X.XX)
** Child development**			
Bayley score *			
Cognitive composite	XX.X (X.X)	XX.X (X.X)	XX.X (X.X)
Language composite	XX.X (X.X)	XX.X (X.X)	XX.X (X.X)
Motor composite	XX.X (X.X)	XX.X (X.X)	XX.X (X.X)
Wolke's behaviour score *			
Approach	X.X (X.X)	X.X (X.X)	X.X (X.X)
Adaptability	X.X (X.X)	X.X (X.X)	X.X (X.X)
General Emotional Tone	X.X (X.X)	X.X (X.X)	X.X (X.X)
Attentiveness	X.X (X.X)	X.X (X.X)	X.X (X.X)
Robustness	X.X (X.X)	X.X (X.X)	X.X (X.X)
Cooperation	X.X (X.X)	X.X (X.X)	X.X (X.X)
Vocalization	X.X (X.X)	X.X (X.X)	X.X (X.X)
Exploration	X.X (X.X)	X.X (X.X)	X.X (X.X)
Enthusiasm	X.X (X.X)	X.X (X.X)	X.X (X.X)
Temperament score			
Positive Emotionality *	XX.X (X.X)	XX.X (X.X)	XX.X (X.X)
Negative Emotionality *	X.X (X.X)	X.X (X.X)	X.X (X.X)
Fear *	X.X (X.X)	X.X (X.X)	X.X (X.X)
Social Approach *	X.X (X.X)	X.X (X.X)	X.X (X.X)
Orientation *	XX.X (X.X)	XX.X (X.X)	XX.X (X.X)
Related to Sleep †	XX.X (X.X-X.X)	XX.X (X.X-X.X)	XX.X (X.X-X.X)
Related to Energy and Exploration †	XX.X (X.X-X.X)	XX.X (X.X-X.X)	XX.X (X.X-X.X)

MNPs, multiple micronutrient powders. Percentages may not total 100 because of rounding. *Values are mean (SD). †Values are median (25th to 75th percentile).

### Multiple testing adjustment

The two primary comparisons of interest for the primary and key secondary outcomes are iron versus placebo and MNPs versus placebo. We will use a Bonferroni adjustment combined with a gatekeeping procedure to ensure control of the Type I error rate for the primary outcome across all three pairwise comparisons. Using the Bonferroni correction, we will test each of the two primary null hypotheses of no difference between iron and placebo and MNPs and placebo for the primary outcome at the two-sided 2.5% level of significance. If at least one of the two primary null hypotheses can be rejected (multiplicity unadjusted P-Value < 0.025), a comparison of iron versus MNPs will take place at either the two-sided 2.5% (if either iron or MNPs is superior to placebo) or 5% level of significance (if both iron and MNPs are superior to placebo). Estimates and two-sided confidence intervals will be presented with the same level of significance as used for the testing of these null hypotheses, along with multiplicity unadjusted and adjusted P-Values. If neither iron nor MNPs is superior to placebo, we will report the estimate and two-sided 95% confidence interval but not the P-Value for the comparison of iron versus MNPs.

For the set of key secondary outcomes, we will use the Hochberg procedure for each of the three pairwise comparisons at the level of significance used for the primary outcome only if the corresponding null hypothesis is rejected for the primary outcome. No multiplicity adjustment is planned for secondary and exploratory outcomes, and no P-Values will be presented.

We will follow the above outlined multiple testing approach for the primary and key secondary outcomes both for the primary time-point at month 3 and the secondary time-point at month 12 separately. The primary objective of the trial will have been met if one of the two primary null hypotheses for the primary outcome at the primary time-point can be rejected at the predetermined significance level. 

### Efficacy (including selected laboratory) outcomes: analysis

A constrained longitudinal data analysis method proposed by Liang and Zeger
^
16
^ will be used to examine the primary outcome (Bayley III cognitive composite score at baseline, 3 months and 12 months post-baseline). The model will incorporate study visit as a categorical variable, treatment and treatment by study visit interaction and adjust for the stratification randomisation factors (union and sex) as main effects. The model will assume a common baseline mean across the three treatment arms and an unstructured variance-covariance among the repeated measurements. In case of non-convergence, we will consider alternative structures (first-order autoregressive, Toeplitz, compound symmetry). The treatment effect will be estimated from this model as the difference between two treatments in mean change from baseline to 3 months post-intervention (
Table 2).

**Table 2. T2:** Primary, key secondary, and secondary outcomes, according to treatment group (intention-to-treat population).

Assessment	Iron (N=XXXX)		MNPs (N=XXXX)		Placebo (N=XXXX)		Iron vs. Placebo			MNPs vs. Placebo			Iron vs. MNPs		
	no. of children measured	Mean (SD) *	no. of children measured	Mean (SD) *	no. of children measured	Mean (SD) *	Estimate (CI) †	P Value Unadjusted	P Value Adjusted †	Estimate (CI) †	P Value Unadjusted	P Value Adjusted †	Estimate (CI) †	P Value Unadjusted	P Value Adjusted †
Month 3															
Primary endpoint															
Bayley score															
Change in cognitive composite score	XXXX	X.X (X.X)	XXXX	X.X (X.X)	XXXX	X.X (X.X)	X.X (X.X to X.X)	0.XXX	0.XXX	X.X (X.X to X.X)	0.XXX	0.XXX	X.X (X.X to X.X)	0.XXX	0.XXX
Key secondary endpoints															
Bayley score															
Change in language composite score	XXXX	X.X (X.X)	XXXX	X.X (X.X)	XXXX	X.X (X.X)	X.X (X.X to X.X)	0.XXX	0.XXX	X.X (X.X to X.X)	0.XXX	0.XXX	X.X (X.X to X.X)	0.XXX	0.XXX
Change in motor composite score	XXXX	X.X (X.X)	XXXX	X.X (X.X)	XXXX	X.X (X.X)	X.X (X.X to X.X)	0.XXX	0.XXX	X.X (X.X to X.X)	0.XXX	0.XXX	X.X (X.X to X.X)	0.XXX	0.XXX
Anthropometric indices															
Change in length-for-age z-score	XXXX	X.X (X.X)	XXXX	X.X (X.X)	XXXX	X.X (X.X)	X.X (X.X to X.X)	0.XXX	0.XXX	X.X (X.X to X.X)	0.XXX	0.XXX	X.X (X.X to X.X)	0.XXX	0.XXX
Change in weight-for-age z-score	XXXX	X.X (X.X)	XXXX	X.X (X.X)	XXXX	X.X (X.X)	X.X (X.X to X.X)	0.XXX	0.XXX	X.X (X.X to X.X)	0.XXX	0.XXX	X.X (X.X to X.X)	0.XXX	0.XXX
Laboratory indices															
Change in haemoglobin concentration (g/L)	XXXX	X.X (X.X)	XXXX	X.X (X.X)	XXXX	X.X (X.X)	X.X (X.X to X.X)	0.XXX	0.XXX	X.X (X.X to X.X)	0.XXX	0.XXX	X.X (X.X to X.X)	0.XXX	0.XXX
Ferritin (µg/L)	XXXX	XX.X (XX.X- XX.X)	XXXX	XX.X (XX.X- XX.X)	XXXX	XX.X (XX.X- XX.X)	X.XX (X.XX to X.XX)	0.XXX	0.XXX	X.XX (X.XX to X.XX)	0.XXX	0.XXX	X.XX (X.XX to X.XX)	0.XXX	0.XXX
Secondary endpoints															
Anthropometric indices															
Stunting	XXXX	XX (X.X%)	XXXX	XX (X.X%)	XXXX	XX (X.X%)	X.XX (X.XX to X.XX)			X.XX (X.XX to X.XX)			X.XX (X.XX to X.XX)		
Underweight	XXXX	XX (X.X%)	XXXX	XX (X.X%)	XXXX	XX (X.X%)	X.XX (X.XX to X.XX)			X.XX (X.XX to X.XX)			X.XX (X.XX to X.XX)		
Change in weight-for- lenght z-score	XXXX	X.X (X.X)	XXXX	X.X (X.X)	XXXX	X.X (X.X)	X.X (X.X to X.X)			X.X (X.X to X.X)			X.X (X.X to X.X)		
Wasting	XXXX	XX (X.X%)	XXXX	XX (X.X%)	XXXX	XX (X.X%)	X.XX (X.XX to X.XX)			X.XX (X.XX to X.XX)			X.XX (X.XX to X.XX)		
Change in head circumference	XXXX	X.X (X.X)	XXXX	X.X (X.X)	XXXX	X.X (X.X)	X.X (X.X to X.X)			X.X (X.X to X.X)			X.X (X.X to X.X)		
Laboratory indices															
Anaemia	XXXX	XX (X.X%)	XXXX	XX (X.X%)	XXXX	XX (X.X%)	X.XX (X.XX to X.XX)			X.XX (X.XX to X.XX)			X.XX (X.XX to X.XX)		
Iron deficient	XXXX	XX (X.X%)	XXXX	XX (X.X%)	XXXX	XX (X.X%)	X.XX (X.XX to X.XX)			X.XX (X.XX to X.XX)			X.XX (X.XX to X.XX)		
Iron deficient anaemia	XXXX	XX (X.X%)	XXXX	XX (X.X%)	XXXX	XX (X.X%)	X.XX (X.XX to X.XX)			X.XX (X.XX to X.XX)			X.XX (X.XX to X.XX)		
Month 12															
Primary variable															
Change in cognitive composite score	XXXX	X.X (X.X)	XXXX	X.X (X.X)	XXXX	X.X (X.X)	X.X (X.X to X.X)	0.XXX	0.XXX	X.X (X.X to X.X)	0.XXX	0.XXX	X.X (X.X to X.X)	0.XXX	0.XXX
Key secondary variables															
Bayley score															
Change in language composite score	XXXX	X.X (X.X)	XXXX	X.X (X.X)	XXXX	X.X (X.X)	X.X (X.X to X.X)	0.XXX	0.XXX	X.X (X.X to X.X)	0.XXX	0.XXX	X.X (X.X to X.X)	0.XXX	0.XXX
Change in motor composite score	XXXX	X.X (X.X)	XXXX	X.X (X.X)	XXXX	X.X (X.X)	X.X (X.X to X.X)	0.XXX	0.XXX	X.X (X.X to X.X)	0.XXX	0.XXX	X.X (X.X to X.X)	0.XXX	0.XXX
Anthropometric indices															
Change in length-for-age z-score	XXXX	X.X (X.X)	XXXX	X.X (X.X)	XXXX	X.X (X.X)	X.X (X.X to X.X)	0.XXX	0.XXX	X.X (X.X to X.X)	0.XXX	0.XXX	X.X (X.X to X.X)	0.XXX	0.XXX
Change in weight-for-age z-score	XXXX	X.X (X.X)	XXXX	X.X (X.X)	XXXX	X.X (X.X)	X.X (X.X to X.X)	0.XXX	0.XXX	X.X (X.X to X.X)	0.XXX	0.XXX	X.X (X.X to X.X)	0.XXX	0.XXX
Laboratory indices															
Change in haemoglobin concentration (g/L)	XXXX	X.X (X.X)	XXXX	X.X (X.X)	XXXX	X.X (X.X)	X.X (X.X to X.X)	0.XXX	0.XXX	X.X (X.X to X.X)	0.XXX	0.XXX	X.X (X.X to X.X)	0.XXX	0.XXX
Ferritin (µg/L)	XXXX	XX.X (XX.X- XX.X)	XXXX	XX.X (XX.X- XX.X)	XXXX	XX.X (XX.X- XX.X)	X.XX (X.XX to X.XX)	0.XXX	0.XXX	X.XX (X.XX to X.XX)	0.XXX	0.XXX	X.XX (X.XX to X.XX)	0.XXX	0.XXX
Secondary variables															
Anthropometric indices															
Stunting	XXXX	XX (X.X%)	XXXX	XX (X.X%)	XXXX	XX (X.X%)	X.XX (X.XX to X.XX)			X.XX (X.XX to X.XX)			X.XX (X.XX to X.XX)		
Underweight	XXXX	XX (X.X%)	XXXX	XX (X.X%)	XXXX	XX (X.X%)	X.XX (X.XX to X.XX)			X.XX (X.XX to X.XX)			X.XX (X.XX to X.XX)		
Change in weight-for- lenght z-score	XXXX	X.X (X.X)	XXXX	X.X (X.X)	XXXX	X.X (X.X)	X.X (X.X to X.X)			X.X (X.X to X.X)			X.X (X.X to X.X)		
Wasting	XXXX	XX (X.X%)	XXXX	XX (X.X%)	XXXX	XX (X.X%)	X.XX (X.XX to X.XX)			X.XX (X.XX to X.XX)			X.XX (X.XX to X.XX)		
Change in head circumference	XXXX	X.X (X.X)	XXXX	X.X (X.X)	XXXX	X.X (X.X)	X.X (X.X to X.X)			X.X (X.X to X.X)			X.X (X.X to X.X)		
Laboratory indices															
Anaemia	XXXX	XX (X.X%)	XXXX	XX (X.X%)	XXXX	XX (X.X%)	X.XX (X.XX to X.XX)			X.XX (X.XX to X.XX)			X.XX (X.XX to X.XX)		
Iron deficient	XXXX	XX (X.X%)	XXXX	XX (X.X%)	XXXX	XX (X.X%)	X.XX (X.XX to X.XX)			X.XX (X.XX to X.XX)			X.XX (X.XX to X.XX)		
Iron deficient anaemia	XXXX	XX (X.X%)	XXXX	XX (X.X%)	XXXX	XX (X.X%)	X.XX (X.XX to X.XX)			X.XX (X.XX to X.XX)			X.XX (X.XX to X.XX)		

MNPs, multiple micronutrient powders; CI, confidence interval *Values are mean (SD) or no. (%), with the exception of ferritin which is median (25th to 75th percentile). †Multiplicity-adjusted according to the pre-specified multiple testing strategy.

Continuous key secondary, secondary, and exploratory outcomes will be analysed similarly as the primary outcome. Ferritin (µg/L) will be log
_e_ transformed before analysis. Binary outcomes will be analysed using a generalised linear mixed model with a log-link function and binomial distribution, including child as a random intercept. In case of non-convergence, we will use a logit link function instead.

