### Setting

The trial is conducted in Rupganj, a rural subdistrict/upazila of Narayanganj district about 50 km from Dhaka, in Bangladesh. Three unions (Bhulta, Golakandail, Rupganj) within the subdistrict are included, with each union covered by a dedicated field team.

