### Randomisation and allocation

Children were randomly allocated to one of the three arms with 1:1:1 allocation using a computer-generated schedule of randomly permuted blocks of fixed size stratified by union and sex to achieve balance between the arms within each stratum. The randomisation list was computer-generated by an independent statistician. Blinding of the team visiting the site, the caregiver(s) and study participants was achieved through the use of identical packaging of sachets and syrup. Researchers, caregivers, persons involved with data collection (i.e., field team) or analysis will be blinded to the allocation code until the database has been cleaned and is ready for analysis.

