### Sensitivity analyses

In addition to the analyses specified for the primary, key secondary, and secondary outcomes, the following sensitivity analyses will be applied for these outcomes:

1. Analyses consisting of models adjusted for potential prognostic or predictive variables:

a. Adding to the model adjusted for union and sex, the main effect of family care indicator score (continuous) and maternal education (No education; 1–8 years schooling completed; 9–12 years schooling completed; >12 years schooling completed).b. Adding to the model adjusted for union and sex, the main effect of variables in
Table 1 demonstrating unexpected imbalance between the treatment arms after unblinding.c. Adding to the model adjusted for union and sex, the main effect for rater and the interaction between rater and study visit (only applies to Bayley III, Wolke’s Behaviour rating scale, and temperament questionnaire).d. Adding to the model adjusted for union, sex, family care indicator, and maternal education, the main effect for rater and the interaction between rater and study visit (only applies to Bayley III, Wolke’s Behaviour rating scale, and temperament questionnaire).

2. Analyses of the secondary strategy to handle missing data.

3. Analyses of the model adjusted for union and sex for the per-protocol population defined as randomised children who were compliant to treatment, and without protocol violations (no informed consent or withdrawn informed consent for use of all data, violation in/ exclusion criteria, or improper unblinding of the child’s allocated treatment).

4. Analyses using the Complier Average Causal Effect method to estimate the average effect of treatment among compliers
^
17
^.

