### Subgroup analyses

Exploratory subgroup analyses will be performed for cognitive motor and language composite scores assessed by Bayley III at 3 and 12 months. Subgroup (main effect) and the subgroup-by-treatment-by-visit interaction (as well as subgroup-by-treatment and subgroup-by-visit interaction) terms will be added to the constrained longitudinal data analysis model to evaluate whether the treatment effect differs between subgroup categories. The following subgroups will be explored: sex (male/female), baseline anaemia status (yes/no), baseline iron deficient status (yes/no), baseline iron deficient anaemia status (yes/no), baseline stunting (yes/no), baseline home stimulation as measured by the family care indicator questionnaire (below/ above median family care indicator total score), baseline household food insecurity status (yes/no), baseline wealth status (below/ above median wealth index score), and union (Bhulta, Golakandail, Rupganj). No multiplicity adjustments are planned for the subgroup analyses due to their explorative nature, we will present the estimates and two-sided 95% confidence interval along with (multiplicity unadjusted) P-Values. Results of the subgroup analyses will be displayed using Forest plots.

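### The primary model holds union and sex effects equal at every visit; if they change between visits, the reported confidence intervals are slightly too wide (low-priority refinement, not a validity error)

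*SAP article*

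**What the plan says.** The section on efficacy analysis makes visit and treatment the only factors whose effects may vary over time: "The model will incorporate study visit as a categorical variable, treatment and treatment by study visit interaction". Union and sex enter differently. The model will "adjust for the stratification randomisation factors (union and sex) as main effects", with a common baseline mean across arms and "an unstructured variance-covariance among the repeated measurements". The same section extends this approach to the continuous key secondary, secondary and exploratory outcomes. The safety section extends it to C-reactive protein.

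Union and sex are design factors. Allocation used "1:1:1 allocation using a computer-generated schedule of randomly permuted blocks of fixed size stratified by union and sex". Under Setting, the three unions are described "with each union covered by a dedicated field team", and the blinding text names the field team as the people who collect data.

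Terms that let an assessor effect differ by visit appear only under Sensitivity analyses. Items 1c and 1d add "the main effect for rater and the interaction between rater and study visit", and only for Bayley III, the Wolke behaviour scale and the temperament questionnaire.

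**The concern.** A month-3 regression with baseline as a covariate would estimate the union and sex differences at month 3 freely. Here baseline is a response, so a main effect removes only the part of a union or sex difference that is the same at 8, 11 and 20 months of age. Any change between visits is left in the residual variance.

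This could arise because union is also a marker for the local field team. If one team scores or measures higher at month 3 than at baseline, relative to the others, the model has no term for it. The arms are balanced within union and sex, so the shift cancels from the treatment contrast. It still enlarges the estimated residual variance, and so the standard error. At stake is a slightly conservative primary test, which also gates the key secondary tests, and slightly wide intervals for the continuous outcomes.

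**Working it through.** **Inputs from the SAP article (Sample size):** target difference 2 points; SD 15; two-sided 2.5% per comparison, so z = 2.2414; 1100 per arm with 20% loss, so 1100 × 0.8 = 880 evaluable per arm.

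**Assumptions, not in the document:** equal within-child correlation r between any two visits, 0.2 to 0.6; 15 taken as the SD within union; unions of equal size; union shifts of -d, 0 and +d at month 3 only.

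**Step 1, reference without drift.** The plan gives no drift figure, so the starting point is its power statement. Without using baseline, SE = 15 × √(2/880) = 0.7151 and power = Φ(2/0.7151 − 2.2414) = 71%. With baseline as a response, the variance of the month-3 contrast is 2 × (S33 − S03²/S00)/880, where 0 denotes baseline and 3 month 3. At r = 0.4, S33 − S03²/S00 = 225 × (1 − 0.16) = 189, SE = √(2 × 189/880) = 0.6554 and power = Φ(3.0516 − 2.2414) = 79.1%. The stated 80% needs r of about 0.42. That is a separate matter.

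**Step 2, what a main effect leaves behind.** With equal correlations, the fitted union offset is the average over the three visits, one third of the shift. The misfit is therefore −1/3, +2/3 and −1/3 of the shift at the three visits. The mean squared shift over unions is q = 2d²/3. The residual covariance the model estimates is then:
- S00 = 225 + q/9
- S03 = 225r − 2q/9
- S33 = 225 + 4q/9

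**Step 3, example with d = 4, r = 0.4.** q = 10.667, giving S00 = 226.185, S03 = 87.630 and S33 = 229.741. The conditional variance is 229.741 − 87.630²/226.185 = 195.79. The variance ratio is 195.79/189 = 1.036, and the SE is 0.6671 against 0.6554, or 1.8% wider.

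**Step 4, range of interval widening.**

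| d | r = 0.2 | r = 0.4 | r = 0.6 |
|---|---|---|---|
| 2 | 0.3% | 0.5% | 0.7% |
| 4 | 1.3% | 1.8% | 2.7% |
| 6 | 2.9% | 3.9% | 6.0% |

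At r = 0.4 and d = 4, drift that persists to month 12 inflates the variance by 2.0% (SE √1.020, +1.0%). Drift that reverses at month 12 inflates it by 5.6% (SE √1.056, +2.8%).

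**Step 5, simulation.** 250 runs per scenario, 880 per arm, r = 0.4 with a weaker baseline to month-12 correlation. The mean estimate stayed within about 0.03 points of the true zero in both models. The actual spread of the estimates was practically the same with and without the interactions (0.645 and 0.646 at d = 5; 0.674 and 0.670 at d = 10). The reported SE differed:

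| d | Main effects only | With union-by-visit and sex-by-visit |
|---|---|---|
| 0, 3, 5, 10 | 0.655, 0.662, 0.675, 0.727 | 0.654 to 0.655 throughout |

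With no drift the ratio of the two SEs is 1.0004, so the extra terms cost practically nothing.

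**Step 6, power at r = 0.4.** Because only the reported SE grows, power is Φ((2 − 2.2414 × reported SE)/0.6554).
- d = 4: (2 − 2.2414 × 0.6671)/0.6554 = 0.770, or 77.9%.
- d = 6, reported SE 0.6812: (2 − 2.2414 × 0.6812)/0.6554 = 0.722, or 76.5%.

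Treating the actual spread as inflated too would give 77.5% and 75.6%, which slightly overstates the loss.

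**The case against.** The strongest reply is that nothing here is wrong. Both stratification factors are in the model, as the general principles require, and a prespecified, slightly conservative analysis is valid. That stands, and it sets the priority.

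The drift is also hypothetical, which stands too. The article reports no drift and does not place Bayley raters within single unions. Analysis 1c adds rater to a model that already contains union, so the plan treats the two as distinct. If raters work across unions, union-by-visit would not capture rater drift.

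The shifts needed are large. d = 2 is a 4-point spread between unions, twice the target effect, yet it widens intervals by under 1%. d = 6 is a 12-point spread. If the SD of 15 already includes such variation, planned power is not eroded and only a small gain is forgone. The sex part has not been quantified. It may be small, since the growth z-scores are sex-specific and the Bayley scores are scaled for age.

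Analyses 1c and 1d would show scorer drift in the Bayley scores. That answers part of the point. They do not decide the primary test, and they leave out growth and laboratory outcomes.

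A reader might take the "subgroup-by-treatment and subgroup-by-visit interaction" terms in the subgroup models as an admission that teams drift. They are not: these are the lower-order terms that a three-way interaction requires, included for every subgroup.

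**Conclusion.** The point holds as a low-priority improvement. The main-effects form forces union and sex differences to be equal at all three visits. If they are not equal, the reported intervals are too wide for the stratified design and the test is conservative.

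Under the assumptions above, the widening is about 0.3% to 0.7% at d = 2, 1.3% to 2.7% at d = 4 and 2.9% to 6.0% at d = 6. No drift size can be taken from the article, and no size is given here for growth or laboratory outcomes or for sex.

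Two stronger readings are tempting. One is that the treatment effect is biased or the type I error inflated. Stratified allocation and the simulation both speak against that. The other is that the estimate itself loses precision. Its actual variability is practically unchanged, and only the reported standard error grows.

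**What to change.** Before the allocation code is broken, state that the primary model, and the continuous-outcome models built on it, include union-by-visit and sex-by-visit interactions as well as the main effects. Keep the common-baseline constraint on treatment and the unstructured covariance. Keep rater-by-visit as a sensitivity analysis.

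The cost is one line of text and six parameters: (3 − 1) × (3 − 1) = 4 for union and (2 − 1) × (3 − 1) = 2 for sex, in a trial of 3300 children. No new data are needed. The section on changes from the registry and protocol allows tracked changes before unblinding to count as planned analyses.

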### Sample size

The sample size for the trial was to recruit 3300 children (1100 per treatment arm) in order to have 80% power to detect a two-point difference in Bayley III composite cognitive score between the iron supplementation and placebo arm and the MNPs and placebo arm (two-sided 2.5% level of significance per comparison), assuming a standard deviation of 15 and a 20% loss to follow up after 3 months of intervention. No interim analyses to stop the trial early were planned, and no interim analysis was conducted.

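### The fallback covariance structures assume equal variances and, for two of them, equal visit spacing, with no robust standard error; if used, intervals could be too wide or too narrow

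*SAP article*

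**What the plan says.** The section on the efficacy analysis fits a constrained longitudinal model to scores measured "at baseline, 3 months and 12 months post-baseline". Visit is categorical, and "The model will assume a common baseline mean across the three treatment arms". The planned covariance is "an unstructured variance-covariance among the repeated measurements", which is sound for three unevenly spaced visits. The contingency rule is: "In case of non-convergence, we will consider alternative structures (first-order autoregressive, Toeplitz, compound symmetry".

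The rule names no heterogeneous-variance version, no version based on time distance, no order of choice and no robust standard error. The model also carries the other continuous endpoints: "Continuous key secondary, secondary, and exploratory outcomes will be analysed similarly as the primary outcome". The multiple-testing section applies formal tests at month 3 (primary) and, separately, at month 12.

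**The concern.** Children enter at 8 months of age and are measured again at about 11 and 20 months. In standard form, the three fallback structures restrict the covariance as follows:

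- All three assume the same variance at all three ages.
- First-order autoregressive and Toeplitz, indexed by visit order, make the 0 to 3 month correlation equal to the 3 to 12 month correlation, although the gaps are 3 and 9 months.
- Compound symmetry makes all three correlations equal.

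The standard error of the month-3 contrast depends on the month-3 variance and the baseline to month-3 correlation. The month-12 contrast depends in the same way on the month-12 quantities. If the structure gets these wrong and the standard errors are model-based, the stated confidence level and the 2.5% significance level no longer hold. The confirmatory test is among those affected.

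**Working it through.** The plan gives no figure for the fallback, so there is none to reproduce. The check compares the model-based standard error with the true one under assumed covariances.

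**Inputs from the plan.** 1100 children per arm, 20% loss by month 3 (880 per arm), two-sided 2.5% per comparison (critical value 2.2414), visits at 0, 3 and 12 months. The only variability figure is in the sample size section: "assuming a standard deviation of 15 and a 20% loss to follow up after 3 months of intervention".

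**Assumptions.** Visit-specific SDs and correlations; a further 5% lost before month 12 (1100 × 0.75 = 825 per arm); loss completely at random.

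**Method.** For each assumed true covariance, find the version of each fallback structure that maximises the expected Gaussian likelihood. Then compute the ratio of model-based SE to true SE for an arm contrast in the three-arm constrained model. A ratio above 1 means the interval is too wide; below 1, too narrow. Actual error rate = 2 × [1 − Φ(2.2414 × ratio)].

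**Hand check at month 3.** Take SD 15 at every visit and correlations 0.5 (0 to 3 months), 0.3 (3 to 12) and 0.3 (0 to 12). The fitted autoregressive correlation is 0.403.

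- Unstructured SE: √[2 × 225 × (1 − 0.5²) / 880] = 0.619.
- SE reported by the autoregressive model: √[2 × 225 × (1 − 0.403²) / 880] = 0.654.
- True SE of that estimate: √[2 × 225 × (1 + 0.403² − 2 × 0.403 × 0.5) / 880] = 0.623.
- Ratio: 0.654 / 0.623 = 1.05.

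**Results with correlations 0.5/0.3/0.3** (each cell lists autoregressive, Toeplitz, compound symmetry):

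| Assumed SDs at 0/3/12 months | Month-3 ratio | Month-12 ratio | Actual error, month 3 | Actual error, month 12 |
|---|---|---|---|---|
| 15/15/15 | 1.050, 1.050, 1.061 | 1.020, 0.997, 0.969 | 1.7% to 1.9% | 2.2% to 3.0% |
| 13/15/17 | 1.039, 1.038, 1.046 | 0.887, 0.874, 0.858 | 1.9% to 2.0% | 4.7% to 5.5% |
| 10/10/13 | 1.159, 1.158, 1.168 | 0.858, 0.844, 0.828 | 0.9% | 5.4% to 6.4% |
| 17/15/13 | 1.069, 1.069, 1.087 | 1.206, 1.169, 1.115 | 1.5% to 1.7% | 0.7% to 1.2% |
| 12/15/12 | 0.900, 0.902, 0.906 | 1.098, 1.071, 1.053 | 4.2% to 4.4% | 1.4% to 1.8% |

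The month-12 shortfall comes mostly from the common variance. With SDs 13/15/17 the autoregressive fit uses an SD of 14.87 at every visit, and 14.87 / 17 = 0.87, close to the ratio of 0.887.

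**Wider grid.** Over 28 assumed truths (seven SD patterns by four correlation patterns), the three structures together gave ratios from 0.86 to 1.35 at month 3 and from 0.80 to 1.31 at month 12. The errors at the two visits had opposite signs in 17 to 19 of the 28, depending on the structure.

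**Alternatives on the same grid.** Heterogeneous variances with a time-distance correlation gave 0.97 to 1.00 at month 3 and about 1.00 at month 12. Heterogeneous Toeplitz gave 0.98 to 1.11 and 0.99 to 1.05. A sandwich standard error gives 1.00 in large samples under any structure.

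**The case against.** The strongest reply is that the rule will almost never operate. The planned structure is the right one, it has only six parameters, and 3300 children were to be recruited. The text says only that alternatives will be considered, so it commits to none of the three. This stands, and it keeps the point small. It does not remove the point: a contingency rule should be sound when it is called on, and leaving the choice open among three structures with the same variance restriction is no safeguard.

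A second reply is that equal SDs are a natural working case, because Bayley raw totals are converted to age-based scores and growth is expressed as age- and sex-specific z-scores. On that basis the month-3 error is small and conservative, and the larger figures come from SDs that appear nowhere in the plan. This also stands, so those figures show what could happen and are not forecasts. The same model also serves haemoglobin, log-transformed ferritin and head circumference, for which the plan describes no such standardisation.

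A third reply is that an article may leave optimiser settings and structure variants to the full plan. That is fair for what is unsaid. The three named structures, however, are a stated choice.

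The planned multiple imputation, done in wide format and by arm, imposes none of these structures when filling in scores. It is only a partial check, because the imputed data are then analysed with the same models.

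**Conclusion.** The point holds as a minor one. The named fallback can misstate standard errors at both tested time-points, and nothing in the rule guards against it. The direction and size cannot be known from the plan. With correlations 0.5/0.3/0.3, equal SDs cost about 5% to 6% in width at month 3. A larger month-12 SD makes the month-12 standard error about 11% to 17% too small (error about 5% to 6% at nominal 2.5%). If month 3 had the largest SD, the primary test could also be somewhat liberal (4.2% to 4.4% under SDs 12/15/12).

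Three stronger readings are tempting but not supported:

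- A reader might infer that the intervals would necessarily be wrong in both directions. With falling SDs and these correlations they are too wide at both visits, and with equal SDs the errors are small.
- A reader might infer that the likelihood handling of missing data would be biased. A wrong covariance can cause this, but no bias has been calculated here; the working covers standard errors only.
- A reader might extend the point to every sensitivity analysis. The complier average causal effect analysis is not stated to use this model.

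**What to change.** Reword the contingency rule in the section on the efficacy analysis:

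1. On non-convergence, first change starting values or the optimiser and keep the unstructured matrix.
2. If that fails, move in a stated order to heterogeneous variances with a correlation that depends on time distance, then to heterogeneous Toeplitz.
3. Report empirical (sandwich) standard errors in any fallback.

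Step 3 is needed even with the better structures. With correlations 0.5/0.3/0.3 the time-distance version still gave a month-3 ratio of 0.97, an actual error of about 3.0%. Steps 1 and 2 matter because a sandwich standard error corrects the precision but not any bias from dropout under a wrong covariance. Refitting two visits at a time is not required and would discard information.

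The cost is a few lines of wording and a slightly more complex fallback; no data or design change is involved. The change belongs in the version signed off at the blinded data review, since the plan treats anything later as post hoc.
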